### **8.8 Study Drug Accountability**

The study drugs are shipped to the individual trial sites by the pharmacy of the University Hospital Basel, which keeps the log for each of the numbered packages containing the study medication for one participant. Prednisone and placebo can be shipped at ambient temperature (min. 15°C, max. 25°C). The local study nurse will accept the delivery and store the study medication at room temperature in a locked cabinet, separate from routine stocks.

The Study Medication provided for this study will only be dispensed to enrolled Study Participants and used only

---

as directed in the study protocol. The local Principal Investigators at each Study Site are responsible for all supplies of Study Medication from the time of receipt until destruction of any unused or non-dispensed Study Medication. For this purpose, the Investigator or delegate will keep an accurate Study Medication accountability record and destruction log. At the end of the study, one copy of the Study Medication Accountability record will be sent to the sponsor-investigator and one kept in the Investigator's Site file.

## **8.9 Return or Destruction of Study Drug**

Unused study drugs and packing material will be destroyed by the local pharmacy of each trial site. A certificate thereof will be delivered.

## 9. STUDY ASSESSMENTS

### 9.1 Study flow chart(s) / table of study procedures and assessments

| Study Periods                                                                                                                                                           | Screening  | Treatment, Intervention Period |              |               | Follow-up     |                |                |
|-------------------------------------------------------------------------------------------------------------------------------------------------------------------------|------------|--------------------------------|--------------|---------------|---------------|----------------|----------------|
| Visit                                                                                                                                                                   | 1          | 2                              | 3            | 4             | 5             | 6              | 7 (final)      |
| Time (hour, day, week)                                                                                                                                                  | -7d to -1d | Day 1                          | Day 7
±1d | Day 28
±3d | Day 35
±3d | Day 90
± 5d | Day 180
±7d |
| Patient Information and Informed Consent                                                                                                                                | x          |                                |              |               |               |                |                |
| In- /Exclusion Criteria                                                                                                                                                 | x          |                                |              |               |               |                |                |
| Vital Signs (heart rate, blood pressure), body weight, height [only day 1])                                                                                             |            | x                              | x **         |               | x **          |                |                |
| Laboratory Tests:
250 mcg Synacthen® test                                                                                                                            |            | x                              | x **         |               | x **          |                |                |
| Pregnancy test in menstruating women not taking oral contraceptive                                                                                                      | x          |                                |              |               |               |                |                |
| Randomisation                                                                                                                                                           |            | x                              |              |               |               |                |                |
| Interview Assessment: Primary outcome variables*† - fill out CRF                                                                                                        |            |                                | x            | x             | x             | x              | x              |
| Interview Assessment: Secondary outcome variables*† - fill out CRF                                                                                                      |            |                                | x            | x             | x             | x              | x              |
| Interview Assessment:*†: symptoms & signs of hypocortisolism; concomitant therapy; serious adverse events; therapeutic interventions by other physicians – fill out CRF |            | x                              | x            | x             | x             | x              | x              |
| Dispense and start study medication                                                                                                                                     |            | x                              |              |               |               |                |                |
| Terminate study medication                                                                                                                                              |            |                                |              | x             |               |                |                |
| Return surplus study medication                                                                                                                                         |            |                                |              |               | x††           |                |                |

\* Assessed in all study participants

\*\* Due to restricted resources, assessed only in a subgroup of 180 patients living near their respective trial site.

† Assessed by telephone, except day 1 (all centers) and days 7 and 35 (subgroup of 180 patients that have 2 clinical visits during follow-up). If desired by a trial site, follow-up telephone interviews can be performed centrally by a study coordinator. In these instances, ICF shall be adapted accordingly for such site(s).

†† by mail, except if a clinical visit is performed on day 35.

### 9.2 Assessments of outcomes

#### 9.2.1 Assessment of primary outcome

Assessment tools of 1° outcome measures:

- Questionnaire: Hospitalization? Unplanned glucocorticoid therapy? Adrenal crisis?
- Treating physician interview: Death?

The 1° outcome can be assessed during a telephone interview with the patient using a questionnaire.

If a patient cannot be reached, the treating physician will be contacted to inquire about the possibility of the patient's death.

The 1° outcome will be assessed by telephone on days 7, 28, 35, 90, and 180; ± the variations indicated in the study flow chart. Additionally, a subgroup of 180 patients living near their respective trial site will be seen for a clinical visit on study days 7 and 35. These clinical visits include vital signs (heart rate, blood pressure in recumbent and upright positions), and a 250 mcg Synacthen® test.

### 9.2.2 Assessment of secondary outcomes

The secondary outcomes will be assessed using telephone interviews with patients. Questionnaires will be used to assess outcomes, as described above (see 9.2.) Treating physicians will be contacted by telephone to inquire about the secondary outcomes, cumulative systemic overall glucocorticoid dose, cumulative systemic glucocorticoid dose to treat or prevent adrenal failure, cumulative systemic glucocorticoid dose to treat relapse of underlying disease; as well as the primary outcome component of death, where applicable.

#### Assessment tools of 2° outcome measures:

- Questionnaire: individual components of 1° outcome; SF-12 survey; symptoms of hypocortisolism
- Signs of hypocortisolism, in subgroup as specified in above table: measure blood pressure (supine and standing), measure heart rate.
- Treating physician interview: cumulative systemic overall glucocorticoid dose? Cumulative systemic glucocorticoid dose to treat or prevent adrenal failure? Cumulative systemic glucocorticoid dose to treat relapse of underlying disease?
- Perform 250 mcg ACTH (Synacthen®) test\*: in subgroup as specified in the above table.
- Measure HbA1c value: in subgroup as specified in the above table.
- Determine length of hospital stay (if hospitalized upon study inclusion): Study hospital chart

\*The 250 mcg ACTH (Synacthen®) test is a routine procedure for the assessment of the functional status of the hypothalamus-pituitary-adrenal axis. The test is performed as follows. It can be done at any time during the day without the need of a fasting state. A blood sample is drawn for measurement of baseline serum cortisol. 1 ampoule (250 mcg) of tetracosactide (beta-1-24 – corticotropin; Synacthen®) is injected intravenously. 30 and 60 minutes after the injection, blood samples are drawn for measurement of stimulated serum cortisol.

The 2° outcomes will be assessed by telephone on days 7, 28, 35, 90, and 180. Additionally, a subgroup of 180 patients will be seen for a clinical visit on study days 7 and 35. These clinical visits include vital signs (heart rate, blood pressure while in recumbent and upright position, and a 250 mcg Synacthen® test.

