### 5.2 Secondary Outcomes

1. Time to first occurrence of individual components of the primary outcome;
2. Cumulative overall systemic glucocorticoid dose;
3. Cumulative systemic glucocorticoid dose administered to treat or prevent adrenal failure;
4. Cumulative systemic glucocorticoid dose administered to treat relapse of disease, specified for each disease;
5. General health status as self-assessed by the participant on a visual analog scale (VAS) from 0 to 100, assessed at days 1, 7, 28, 35, 90, 180;
6. Score of symptoms and signs of hypocortisolism: weakness, hypothermia, nausea, vomiting, abdominal pain, fatigue, dizziness (assessed in structured interviews at time points: days 1, 7, 28, 35, 90, 180). Blood pressure (supine and standing) is assessed day 1 in all participants, but due to limited resources only in a subgroup of 180 patients living near their respective study center on days 7 and 35.
7. Performance in 250 mcg ACTH (Synacthen®) test: test assessed day 1 in all participants, plus days 7 and 35 in a subgroup of 180 patients,
8. In patients hospitalized at study entry: length of hospital stay.

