**Patients and Procedures.** In total, 573 patients will be enrolled. Patients will be randomly assigned in a 1:1 ratio to either prednisone in decreasing doses over 4 weeks or placebo using a centralized secured study website, programmed by the CTU Basel, to ensure allocation concealment. Patients, treating physicians, and study personnel will be blinded to treatment allocation to either prednisone or matching placebo. At inclusion, we will perform a 250 mcg ACTH (Synacthen®) stimulation test  $\geq 24$  hrs. after the last glucocorticoid dose to avoid interaction of prednisone with endogenous cortisol. We chose this test because, unlike the low-dose (1 mcg) test, it is widely available and can be performed by personnel of various disciplines. The results of the test will be blinded to treating physicians and investigators, and its value to predict clinical outcome will only be assessed after completion of the trial. As a safety measure, all patients will be instructed about stress coverage as well as signs and symptoms of hypocortisolism and will be provided with emergency medication, as described above (paragraph 5.4). Treating physicians, including those in primary care, will be informed about their patients’ participation in the trial to increase awareness of potentially occurring hypoadrenergic symptoms. Patients will be randomized to the standard (tapering) or the experimental (matching placebo) arm. The rate at which glucocorticoid should be tapered in the standard arm has been extensively discussed among collaborators and other experts from endocrinology and specialties treating prospective study patients (general internists, gastroenterologists, neurologists, pulmonologists). Although ideally chosen for the standard arm in a noninferiority trial, there is no published standard, “best-of-care” glucocorticoid tapering scheme, but a large variety of expert opinions. Also, there are no controlled data indicating the superiority, with respect to clinical outcome of the underlying disease, of one particular tapering scheme over another, or of tapering versus abrupt stopping. Thus, for many inflammatory and autoimmune disorders, there are no specific guidelines as to the tapering regimens. If there are recommendations to taper to a daily dose below 7.5 mg of prednisone equivalent, e.g. in giant cell arteritis, patients with the respective disorder are not eligible for the study. After careful reflection of all these aspects, the planning committee has settled on the regimen depicted in the figure below. Follow-up will be for six months. We do not think that a longer follow-up period is helpful because proportions of patients with suppressed adrenals will be low at six months (2% in our previous REDUCE trial), the necessary sample size does not change appreciably, and loss to follow-up would likely increase.

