
In order to improve adherence to the study and ensure feasibility, follow-up visits in most study centers will be by telephone only. Visits will be performed early after stopping glucocorticoids in both arms (i.e. at days 7 and 35) to ensure safety; the other two visits will be on days 90 and 180. In a subset of 180 patients, we will also perform clinical visits on days 7 and 35.

Figure: Study Algorithm

[figure not shown]

**Days 7 and 35 :** Due to limited resources, clinical visits will be performed only in a subgroup of 180 patients living in vicinity to their respective trial site, including examination of vital signs and 250 mcg synacthen test.

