## **8. STUDY INTERVENTION**

### **8.1 Identity of Investigational Products (treatment / medical device)**

Study drug: prednisone vs. matching placebo.

1. Standard (tapering) arm: patients receive 7.5 mg prednisone/d for 7 days; then 5 mg prednisone/d for 7 days; then 2.5 mg prednisone/d for 7 days; then 2.5 mg prednisone every other day for 7 days, then stop.

2. Intervention (abrupt stop) arm: patients receive matching placebo for 4 weeks, then stop.

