#### **8.1.3 Packaging, Labelling and Supply (re-supply)**

Study drugs will be dispensed in a glass vial labeled according to GMP guidelines, annex 13, in German and French language. Each vial will contain 30 tablets, either verum or placebo.

The identification labels contain the unique Participant Study ID and fulfil the requirements of Annex 13 of the "EUDRALEX Volume 4 - Medicinal Products for Human and Veterinary Use: Good Manufacturing Practice". Label text will be available in local language of the countries of each participating centre (i.e., German,).

Dosing:

Week 1: Take one and one half tablets, either prednisone (verum) or placebo, daily p.o.

Week 2: Take one tablet, either prednisone (verum) or placebo, daily p.o.

Week 3: Take one half tablet, either prednisone (verum) or placebo, daily p.o.

Week 4: Take one half tablet, either prednisone (verum) or placebo, on days 1, 3, 5, and 7 p.o.

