### **9.3.3 Day 7 ± 1d (visit 3)**

A. Telephone interview: Assess VAS for general health status. Fill out CRF. Ask patient about pill count. Schedule visit 3.

B. Clinical visit (subgroup of 180 patients living near their respective trial site): Measure heart rate and blood pressure in recumbent and supine position after at least 5 minutes resting. Perform 250 mcg Synacthen test. Draw blood for reserve serum. For reserve serum: centrifuge sample, pipet serum into 1 ml aliquots, store at -20°C. Schedule visit 4.

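### The 24-hour glucocorticoid-free interval is stated only for the inclusion ACTH test, so day-7 repeat tests can carry the prednisone interaction in the taper arm alone

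*Protocol*

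**What the plan says.** Section 6.1 (Patients and Procedures) introduces the test with the words "At inclusion, we will perform a 250 mcg ACTH (Synacthen®) stimulation test". It requires at least 24 hours "after the last glucocorticoid dose to avoid interaction of prednisone with endogenous cortisol". This is the only place where the interval appears.

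Secondary outcome 7 in section 5.2 covers three occasions: "test assessed day 1 in all participants, plus days 7 and 35 in a subgroup of 180 patients". The test procedure is a footnote in section 9.2.2, attached to the line on the subgroup tests: "It can be done at any time during the day without the need of a fasting state". It mentions no time since the last dose. For the day-7 clinical visit, section 9.3.3 says only "Perform 250 mcg Synacthen test. Draw blood for reserve serum". Sections 9.3.5 (day 35) and 9.2.4.2 (laboratory parameters) are equally silent on timing.

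On dosing, section 8.1 states for the taper arm that "patients receive 7.5 mg prednisone/d for 7 days; then 5 mg prednisone/d for 7 days"; the other arm receives placebo. Section 8.1.3 gives no clock time: "Week 1: Take one and one half tablets, either prednisone (verum) or placebo, daily p.o". Section 6.1 also describes the follow-up visits: "Visits will be performed early after stopping glucocorticoids in both arms (i.e. at days 7 and 35) to ensure safety".

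**The concern.** The protocol names a disturbance of the test and controls it at inclusion. At day 7 the same disturbance is possible again, and no passage controls it. It can occur only in patients taking active tablets, so it lines up with the randomised arm.

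Two uses of the data are exposed. One is secondary outcome 7 at day 7, both between arms and as the taper arm's change from day 1, since the day-1 test carries the interval and the day-7 test need not. The other is the secondary objective in section 4.3 that relates symptoms and signs of hypocortisolism to biochemical performance. If both arms are pooled at day 7, part of the association may reflect how recently a taper-arm patient took prednisone. Test results stay concealed until the trial ends (section 9.2.4.2), so nobody would notice the problem during conduct.

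**Working it through.** The plan states no figure on this point, so the check sets the dosing calendar against the visit windows.

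**Inputs.** Visit windows of day 7 ± 1 and day 35 ± 3, with study medication started on day 1 (section 9.1). Taper-arm dosing from sections 8.1 and 8.1.3: 7.5 mg daily in week 1, 5 mg daily in week 2, 2.5 mg daily in week 3, then 2.5 mg on days 1, 3, 5 and 7 of week 4. Subgroup of 180; allocation 1:1.

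**Taper arm at each visit.**

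| Visit | Study day | Dose scheduled that day | Last scheduled dose | Days since that dose |
|---|---|---|---|---|
| Day 7 | 6 | 7.5 mg | day 6 | 0 |
| Day 7 | 7 | 7.5 mg | day 7 | 0 |
| Day 7 | 8 | 5 mg | day 8 | 0 |
| Day 35 | 32 | none | day 28 | 4 |
| Day 35 | 35 | none | day 28 | 7 |
| Day 35 | 38 | none | day 28 | 10 |

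The last dose falls on day 7 of week 4, which is study day 21 + 7 = 28.

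**Day 7.** A dose is due on every day of the window and on every day before it. A test at an arbitrary time of day therefore falls less than 24 hours after prednisone, unless it happens to come just before a dose that is already due. The abrupt-stop arm has had no study prednisone.

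**Day 35.** The gap is 4 to 10 days, so scheduled dosing meets the 24-hour condition in both arms.

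**Number affected.** 180 × 1/2 = about 90 taper-arm patients, or half of the day-7 tests. The subgroup is 180/573 = 31% of the planned sample.

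**Time since the last active dose.** Section 6.1 puts the abrupt-stop arm's last active dose at least 24 hours before the day-1 test, so its day-7 visit comes about 7 days after stopping. For the taper arm, day 35 − day 28 = 7 days. The existing visits therefore already contain a pair matched on time since the stop.

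**The case against.** **The interval is stated once and perhaps meant throughout.** The day-1 visit list (9.3.2) does not repeat it either, yet there it applies. The any-time-of-day sentence concerns clock time and fasting and does not contradict section 6.1. This is fair: the gap is one of explicitness. It is still a gap, because section 6.1 ties the interval to inclusion, and the footnote a site would follow for the repeat test sets no interval.

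**The day-7 results are not shown to be incomparable.** A reader might infer that they are. The protocol does not support that. Part of any day-7 difference is a real effect of the two regimens, which a 24-hour interval would not remove, and a test just before the daily dose is not forbidden. Section 6.1 speaks of an interaction with endogenous cortisol. It does not mention assay interference, nor does the protocol say that prednisone masks symptoms at day 7.

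**No planned analysis is shown to fail.** Section 11.4.3 names no day-7 comparison between arms. The interaction of test result with arm appears to use the day-1 test. The analysis plan, not at hand, may settle how the repeat tests are used. All of this stands and limits the weight of the point. Outcome 7 at day 7 nevertheless remains a declared outcome.

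**Section 6.1 need not be wrong about the visits.** Its sentence on days 7 and 35 might be taken as false, since the taper arm has not stopped by day 7. It can equally mean day 7 for abrupt stop and day 35 for taper. It is ambiguous.

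**Rescue treatment at day 35.** Under the plan's exponential 40% event rate, 1 − 0.6^(35/180) = 9.5%, or 17 of 180, would have had a primary event by day 35. That figure should not be read as the number of disturbed tests: it counts all primary events, including hospitalisation and death. The number tested soon after open-label glucocorticoid is unknown.

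**Conclusion.** The point holds as a limited flaw in the measurement of one secondary outcome, at one visit, in a subgroup. Followed as written, the protocol lets about 90 of 180 day-7 ACTH tests be done within 24 hours of prednisone, all in the taper arm. The reason to care is the protocol's own: it set the interval at inclusion because of this interaction.

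The figure assumes that the subgroup splits about evenly between arms and that patients take study tablets daily as scheduled. The direction and size of any distortion cannot be derived from the protocol. The primary outcome, the day-1 test, the test-by-arm interaction if it uses day 1, and scheduled day-35 tests are untouched. The change is worth making because it is cheap, not because a main conclusion is at risk.

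**What to change.** - **Timing.** Reconcile sections 6.1, 9.2.2 and 9.3.3 so that the interval of section 6.1 also covers the day-7 test. Schedule that test before the day's study tablets, in the same way in both arms. Doses, regimen and blinding stay as they are. Patients who take their tablets late in the day need a correspondingly later visit for the full interval to have passed.
- **Recording.** Add a case report form field for the time of the last study tablet or other glucocorticoid at each repeat test. Section 8.4 provides a medication diary but does not say that it records clock times.
- **Analysis.** Keep tests that fall inside the interval, flag them, and add a sensitivity analysis without them. Outright exclusion would select on a post-randomisation event whenever rescue treatment is the reason. Report day-7 symptom-cortisol relations by arm, not pooled. As a supplementary analysis, compare abrupt-stop day 7 with taper day 35, which match on time since the last active dose but not on time since randomisation.
- **Wording.** State in section 6.1 which visit follows the stop in which arm.

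The cost is a few sentences, one time field, and subgroup day-7 visits that must be planned around the tablets. Enrolment was scheduled from June 2017, so tests already done cannot be retimed; for these, only flagging is possible, and only where the time of the last dose can be recovered.
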